## Abstract

**Background:**

The 23-valent polysaccharide pneumococcal vaccine (PPV-23) is recommended for elderly and high-risk people, although its effectiveness is controversial. Some studies have reported an increasing risk of acute vascular events among patients with pneumonia, and a recent case-control study has reported a reduction in the risk of myocardial infarction among patients vaccinated with PPV-23. Given that animal experiments have shown that pneumococcal vaccination reduces the extent of atherosclerotic lesions, it has been hypothesized that PPV-23 could protect against acute vascular events by an indirect effect preventing pneumonia or by a direct effect on oxidized low-density lipoproteins. The main objective of this study is to evaluate the clinical effectiveness of PPV-23 in reducing the risk of pneumonia and acute vascular events (related or nonrelated with prior pneumonia) in the general population over 60 years.

**Methods/Design:**

Cohort study including 27,000 individuals 60 years or older assigned to nine Primary Care Centers in the region of Tarragona, Spain. According to the reception of PPV-23 before the start of the study, the study population will be divided into vaccinated and nonvaccinated groups, which will be followed during a consecutive 30-month period. Primary Care and Hospitals discharge databases will initially be used to identify study events (community-acquired pneumonia, hospitalisation for acute myocardial infarction and stroke), but all cases will be further validated by checking clinical records. Multivariable Cox regression analyses estimating hazard ratios (adjusted for age, sex and comorbidities) will be used to estimate vaccine effectiveness.

**Discussion:**

The results of the study will contribute to clarify the controversial effect of the PPV-23 in preventing community-acquired pneumonia and they will be critical in determining the posible role of pneumococcal vaccination in cardiovascular prevention.

## Background

### Epidemiology of pneumococcal infections

Infections caused by *Streptococcus pneumoniae *remain a major public health problem throughout the world. Susceptibility to pneumococcal infections varies with age, being highest in young children and older adults, who experience substantial morbidity and mortality (especially in those with underlying high-risk medical conditions) [1,2].

The main reservoir of pneumococcus is the nasopharynx, and the possible outcomes after colonisation are the clearance by the organism, the asymptomatic persistence for several months (carrier state), or the progression to disease. During the disease the bacteria can spread to adjacent mucosal tissues causing mucosal infections (otitis, sinusitis, bronchitis and pneumonias) or it can invade the bloodstream, or other sterile sites, producing an invasive pneumococcal disease (IPD). In adults, *S. pneumoniae *is the most frequent isolate from clinical samples of respiratory tract infections. It is responsible for approximately 50% of overall cases of community-acquired pneumonia (CAP) in different populations [3-5].

### Pneumococcal vaccination

In the last decades, the need for preventive strategies has driven multiple efforts to develop an effective vaccine, however the existence of more than 90 distinct pneumococcal serotypes has largely complicated the development and evaluation of anti-pneumococcal vaccines. To date, only a 23-valent polysaccharide pneumococcal vaccine (PPV-23) for use in adults and a 7-valent conjugate vaccine for use in infants are available in clinical practice [6-9].

The PPV-23 is generally recommended for high-risk and elderly individuals, but its effectiveness (despite numerous meta-analyses) remains controversial [10-19]. It has been demonstrated that PPV-23 provides considerable protection against invasive pneumococcal disease, while a possible protective effect against pneumonia is discussed [20]. The latest Cochrane Systematic Review supports the use of PPV to prevent IPD in adults, particularly in healthy adults, but it concluded that the meta-analysis does not provide compelling evidence to support the routine use of PPV to prevent pneumonia [18].

### Epidemiological link between pneumonia and acute vascular events

For several decades, there has been data that chronic inflamation can promote atherosclerotic disease,[21] and in recent years some studies have also found data supporting the fact that acute infections (especially influenza and pneumonia) are associated with a transient increasing risk of acute vascular events [22-25]. In fact, it has been reported that a combination of the diagnosis of pneumonia and myocardial infarction is relatively common among patients hospitalised with severe pneumonia [24,25]. Thus, given this data, it has been suggested that pneumococcal vaccination could perhaps protect patients from cardiovascular events [26-28].

Following this, a recent case-control study conducted in Canada has reported a 47% reduction in the risk of acute myocardial infarction (AMI) among subjects who had received the PPV-23, however, the posible cardioprotective effect of pneumococcal vaccination has not still been proved [26].

Theoretically, pneumococcal vaccination could protect against acute cardiovascular events by an indirect effect preventing pneumonia (as the latter has been shown to trigger myocardial infarction), although a direct effect of pneumococcal vaccination on oxidized low- density lipoproteins can not be excluded. In fact, animal experiments have shown that pneumococcal vaccination reduces the extent of atherosclerotic lesions and it has been hypothesized that antibodies directed against Streptococcus pneumoniae would also recognize oxidized low-density lipoprotein and impede the formation of foam cells [29].

The posible effectiveness of PPV-23 to prevent myocardial infarction, if it exists, probably has been overestimated in the aforementioned Canadian report; however, given the prevalence of heart disease worldwide, even a modest protective effect (epidemiologically plausible) would translate into a considerable benefit at the population level [30]. Thus, prospective validations (which will determine whether the cardioprotective effect of vaccination is real and better estimate its true protective efficacy) are greatly needed.

### Use of pneumococcal vaccine in the study area

In Catalonia, a region in the northeast of Spain with a population of seven million people, a publicly funded anti-pneumococcal vaccination programme for all individuals 65 years or older (with or without risk factors) and younger individuals with certain high-risk conditions (basically immunodeficiency, chronic heart or pulmonary disease, diabetes mellitus, severe liver disease or chronic nephropathy) began in October 1999. Further, it was extended for all people 60 years or older in 2002. Since then, a free PPV-23 has been offered when the patients came to the primary care services during the annual influenza vaccination campaigns or in any other visit throughout the year. Some years later, vaccination uptake reached approximately fifty percent,[31] and this provided an excellent opportunity to evaluate the vaccine's effects among the population. The potential effects of vaccination in preventing IPD and pneumonia have been analyzed in our reference population in two prior studies [32,33].

This project proposes a large population-based cohort study with the major aim of evaluating the clinical effectiveness of the PPV-23 against CAP as well as evaluating its potential role in cardiovascular prevention among the general population over 60 years.

## Objectives of the capamis study

The primary objective of the planned study entitled ***CAPAMIS ***is to evaluate the clinical effectiveness of the PPV-23 in the prevention of a first episode of **C**ommunity-**A**cquired **P**neumonia, **A**cute **M**yocardial **I**nfarction and **S**troke among the general population over 60 years. Furthermore, the study will evaluate the effectiveness of PPV-23 in reducing the risk of secondary acute vascular events related with prior pneumonia.

Additional objectives include the evaluation of vaccination effectiveness against severity outcomes (including death, need of ICU admission or length of stay in hospital).

Furthermore, a detailed analysis on population-based data on incidence of myocardial infarction and stroke will be performed in different subsets of the population with certain underlying conditions in order to establish, if it exists, the magnitude of vaccination effectiveness in primary and/or secondary cardiovascular prevention.

In addition to these objectives, the clinical effectiveness of revaccination against different outcomes will be evaluated in the subset of participants who have received more than a dose of PPV-23 prior to the study start or during the study period.

## Methods and Design

### Design, setting and study population

Population-based cohort study focused on adults over 60 years in the region of Tarragona, a mixed residential-industrial urban area in the Mediterranean coast of Catalonia, Spain.

Study subjects include 27,000 community-dwelling adults aged 60 years or more assigned to 9 participating Primary Care Centres (PCCs) in the study area, who will followed during a 30-month consecutive period. Six of the nine participating PCCs are located in Tarragona city (PCC Bonavista, PCC Torreforta, PCC Jaume I, PCC Sant Pere i Sant Pau, PCC Tarraco, PCC Sant Salvador) and three PCCs are located in nearby (less than 12 kilometres from Tarragona) smaller municipalities (PCC Salou, PCC Constanti and PCC Morell). Two reference hospitals for the study population are Hospital Joan XXIII and Hospital Santa Tecla, both located in Tarragona city (which has an overall population of approximately 120,000 all-age inhabitants).

It must be noted that, in Spain, primary care physicians are the first point of call for secondary and tertiary care and all citizens are registered in one PCC.

Inclusion criteria for the CAPAMIS cohort include: a) male or female adults aged 60 years or older as of January 1, 2009; and b) registered in any of the nine PCCs participating at study start. Exclusion criteria include residence in a long-term care facility. Subjects will be identified from primary care information systems. Figure 1 shows the study region and illustrates the location of participating centres.

**Figure 1 F1:**
[figure not shown]
**Research areas of the CAPAMIS Study**. This figure illustrates the geographical distribution of the nine participating Primary Health Care Centers in the region of Tarragona (a mixed residential-industrial urban area, which is located 95 Km from Barcelona, in the mediterranean coast of Catalonia, Spain).

Cohort members will be followed from the beginning of the study (1 January 2009) until occurrence of the first event, the enrolment from the PCC ceases, death, or until the end of the study (30 June 2011).

### Rationale for sample size

The annual incidence of CAP in older adults in the study area is estimated at approximately 10 per 1000 person-year based on prior population-based studies among elderly people in the same study area [34,35]. Incidences of AMI and stroke are estimated in 8 and 12 cases per 1000, respectively, in Spanish population [36,37]. Thus, considering a pneumococcal vaccine coverage of approximately 50%,[31] with a p = 0.05 (two-tailed) the size of the study cohort (N = 27,000 individuals followed during a 30-month period) has an statistical power of 80% to detect a posible vaccination effectiveness of 20% against CAP, a 23% against AMI, a 18% against stroke and a 14% against the combined end-point AMI/stroke.

### Data sources

All participating PCCs have a computerized clinical record system that includes administrative data, medical conditions, prescriptions, laboratory results and registries associated with outpatient visits and diagnoses coded according to the International Classification of Diseases, 10th Revision (ICD-10). This electronic clinical record system will be used to classify vaccination status as well as to identify comorbidities or underlying conditions in cohort members and establish baseline characteristics of the cohort at study start.

During the study period, the primary care electronic registries of the nine participating PCCs will be used as a data source to identify those subjects who have suffered any study event that did not require hospitalisation and were treated as an outpatient during the 30-month study period.

Emergence and hospital diagnosis discharge databases of two reference hospitals (coded according to ICD-9-CM codes (International Classification of Diseases, 9th Revision, Clinical Modification) will be used to identify those cohort members who were admitted to hospital for any study event during the 30-month study period.

A structured data collection instrument will be used to review primary care and hospital clinical records to validate the diagnosis of all cases initially identified by ICD-10 or ICD-9 discharge codes.

### Main outcomes and definitions

The primary endpoints of the *CAPAMIS Study *will be the ocurrence of CAP (hospitalised or outpatient), hospitalisation for AMI, stroke and death from any cause. Table 1 shows definitions and criteria used in collecting primary and secondary outcomes.

**Table 1 T1:** Definitions and criteria used to identify and classify the different endpoints in the *CAPAMIS *Study.

OUTCOMES	DEFINITIONS
**A. Community-acquired pneumonia (CAP)***	Pneumonia will be considered when a new radiological infiltrate is identified in a patient with one major criterion (cough, expectoration or fever) or two minor criteria (dyspnea, pleuritic pain, altered mental status, pulmonary consolidation on auscultation and leukocytosis).

**A1. Hospitalised CAP**	Will be considered those pneumonia cases identified on the basis of the listed primary diagnosis codes in hospital discharge databases (ICD-9-CM codes for pneumonia: 480 to 487.0).

**A2. Outpatient CAP**	Will be considered those CAP cases non-hospitalised, and they will be identified from primary care or emergency visits (not hospitalised) with a code registered for pneumonia in the Emergency Unit discharge codes databases (ICD-9-CM codes: 480 to 487.0) or Primary Care Centers diagnosis database (ICD-10 codes: J10.9, J11.9 and J12 to J18).

**B. Pneumococcal CAP****	Defined as a patient with CAP from whom Streptococcus Pneumoniae is identified by blood culture, sputum culture or urinary antigen.

**B1. Bacteremic pneumococcal CAP**	Will be considered when S. pneumoniae was isolated from blood specimens or other sterile sites.

**B2. Nonbacteremic pneumococcal CAP**	Will be considered when the patients have a typical clinical syndrome of pneumonia without bacteremia (negative or not performed blood culture), but they have a sputum culture that yielded pneumococci with no other likely bacterial pathogens and/or they have positive Binax-NOW Streptococcus pneumoniae urinary antigen test.

**C. Acute myocardial infarction (AMI)**	Defined as a patient hospitalised with diagnosis of acute or recurrent episode of myocardial infarction. Cases will be identified on the basis of the primary and secondary listed diagnosis codes in the hospital discharge database (ICD-9-CM code for AMI: 410). All initially identified cases of AMI will be further validated by checking hospital medical records, and each case will be classified as related or nonrelated with a prior episode of CAP.

**C1. CAP-related episode of AMI**	Defined as AMI ocurring within the first 30 days after the onset of an episode of CAP.

**C2. CAP-nonrelated episode of AMI**	Case of AMI ocurring more than 30 days after an episode of CAP or in a patient without history of prior CAP.

**D. Hospitalisation for stroke**	Defined as a patient admitted to hospital with a diagnosis of stroke, ictus or cerebral infarction. Cases will be identified on the basis of the primary and secondary listed diagnosis codes in the hospital discharge databases (ICD-9-CM codes for stroke: 430 to 437). Haemorragic strokes (codes 430 to 432) and ischaemic strokes will be considered (codes 433, 434, 436 or 437), but transient ischaemic attacks (code 435) will be excluded for the analyses. All cases initially identified of stroke will be further validated by checking hospital medical records, and each case will be classified as related or nonrelated with a prior episode of CAP.

**D1. CAP-related episode of stroke**	Defined as an episode of stroke ocurring within the first 30 days after the onset of CAP.

**D2. CAP-nonrelated episode of stroke**	Defined as an episode of stroke ocurring more than 30 days after an episode of CAP or in a patient without history of a prior episode of CAP.

**E. All-cause death**	It includes patients who died for any cause during the study period. Cases will be identified from primary care information system of each participating PCC.

**E1. Death from CAP**	Defined as a patient who died (in hospital or not) within the first 30-days after the onset of CAP.

**E2. Death from AMI**	Defined as a patient who died within hospital stay or within the first 30-days after the diagnosis of AMI.

**E3. Death from stroke**	Defined as a patient who died within hospital stay or within the first 30 days after the onset of the stroke.

* All cases of CAP (hospitalised and outpatient) must be radiographically confirmed and validated by checking the clinical record with the use of a standardized data-collection instrument. CAP will be considered if, on conclusion of the medical record review, the physician reviewer verified this diagnosis and it was not a readmission, nosocomial pneumonia or another diagnosis.

** Pneumococcal CAP will initially be identified on the basis of ICD-9-CM codes for pneumococcal bacteraemia (codes 038.0, 038.2, 041.0, 041.2) or pneumococcal pneumonia (code 481) in the Hospitals and Emergency discharge diagnosis databases and ICD-10 code for pneumococcal pneumonia (code J13) in the Primary Care visits diagnosis databases. Laboratory records will also be used to identify cases of pneumococcal infections not detected in ICD-9-CM or ICD-10 discharge codes.

The occurrence of CAP will be established on the basis of an acute respiratory illness, with evidence of the presence of a new infiltrate in a chest radiograph.

Outpatient CAP will be identified from primary care or emergency visit (not hospitalised) with a code registered for pneumonia in the PCCs diagnoses databases (ICD-10 codes: J10.9, J11.9, J12 to J18) or in Emergency discharge databases (ICD-9-CM codes: 480 to 487.0). Hospitalisations for CAP will be identified on the basis of the listed primary diagnosis codes in the hospital discharge databases (ICD-9-CM codes 480 to 487.0).

All cases of CAP (hospitalised and outpatient) must be radiographically confirmed and validated by checking the clinical record with the use of a standardized data-collection instrument (which includes sociodemographical, clinical, exploratory, analytical and radiographical data at the time of diagnosis). CAP will be considered if, on conclusion of the medical record review, the physician reviewer verified this diagnosis and it was not a readmission, a nosocomial pneumonia or another diagnosis. Pneumonia severity index (PSI) and the simpler severity rule CURB-65 will be calculated according to criteria described in classical studies [38,39].

Hospitalisation for AMI will be initially identified on the basis of listed primary and secondary diagnosis codes in the reference hospital discharge database (ICD-9-CM code: 410).

Hospitalisation for stroke will also be initially identified on the basis of the listed primary and secondary diagnosis codes in hospital discharge databases (ICD-9-CM codes 430 to 437). Ischaemic strokes (codes 433, 434, 436 or 437) and hemorrhagic strokes (codes 430 to 432) will be considered, but transient ischemic attacks (code 435) will be excluded for the analyses.

All cases of AMI and stroke will be further validated by checking hospital medical records with a standardized data-collection instrument that includes clinical characteristics of the events, and they will be classified as "CAP-related" (occurring within 30 days after onset of pneumonia) or "CAP-nonrelated" (ocurring more than 30 days after an episode of pneumonia or ocurring among patients who have not suffered a previous CAP).

Because of the size of the study, an active following of study participants is not feasible. Nevertheless, the nine PCCs and two reference hospitals provide daily care to the inhabitants living in the selected study area, and they basically apply similar diagnostic checklist and treatment for patients presenting with a clinical suspicion of pneumonia, myocardial infarction or cerebrovascular accident.

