### Statistical analysis

Absolute numbers, means and percentages will be computed to describe the patient population. The differences between groups will be evaluated using the chi-squared or Fisher's test for categorical variables, and the two tailed Student's test or ANOVA for continuous variables as appropriate.

The crude association between the outcomes and vaccination will be evaluated using incidence rates among vaccinated and unvaccinated subjects. The incidence of each event will be calculated as person-year considering in the denominator the sum of person-time contributed to each individual during study period.

Multivariable Cox proportional hazards models with time-varying covariates will be used to calculate hazards ratio (HR) and estimate the association between having received the pneumococcal vaccine and the time of the first outcome event during the study period. Repeated episodes will not be included in the analyses. Vaccine effectiveness will be estimated as (1 - HR) × 100.

Pneumococcal vaccination status will be a time-varying condition (e.g., individuals vaccinated after the beginning of the study) and persons will be considered to be vaccinated 14 days after vaccine administration. Annual influenza vaccine status will also be a time-varying covariate, whereas the other covariates will be defined at study start.

It will be checked for confounders, interactions and multicollinearity among the independent variables. The final models will be adjusted by all significant variables, as well as confounders and other baseline covariables judged of having clinical importance. The proportional hazards assumptions will be assessed adding the covariate by log-time interactions to the model and plotting the scaled and smoothed Schoenfeld residuals obtained from main effects model was possible [40]. Statistical significance will be set at p < 0.05 (two-tailed). The analyses will be performed using Stata/SE Version 9.1. (Stata Corp.)

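### Pneumococcal CAP is counted only if a test is done, and routine care need not test every CAP case, so the HR for this secondary outcome may mix vaccine effect with testing

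*Protocol article*

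**What the plan says.** All points are from the protocol article.

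- **Definition of B.** Table 1 under Main outcomes and definitions: "Defined as a patient with CAP from whom Streptococcus Pneumoniae is identified by blood culture, sputum culture or urinary antigen".
- **Testing is not universal.** Table 1 B2 covers patients with a "typical clinical syndrome of pneumonia without bacteremia (negative or not performed blood culture"), so an absent blood culture and a negative one are treated alike there.
- **What every CAP case must have.** "All cases of CAP (hospitalised and outpatient) must be radiographically confirmed and validated by checking the clinical record". No microbiological test is on that list, and CAP includes outpatient cases found through primary care and emergency visits.
- **How pneumococcal cases are found.** Diagnosis codes come first, and then "Laboratory records will also be used to identify cases of pneumococcal infections not detected in ICD-9-CM or ICD-10 discharge codes". These are records of tests that clinicians chose to order.
- **Follow-up.** "Because of the size of the study, an active following of study participants is not feasible". The article adds that the centres and hospitals serve the same area and that "they basically apply similar diagnostic checklist and treatment for patients presenting with a clinical suspicion of pneumonia".
- **Analysis.** Statistical analysis plans Cox models for time to the first outcome event, and "Vaccine effectiveness will be estimated as (1 - HR) × 100". Pneumococcal and influenza vaccination are time-varying. All other covariates are fixed at study start.

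B is not among the named primary endpoints (CAP, AMI, stroke, all-cause death) and the Objectives do not name it. As a Table 1 entry it is a secondary outcome.

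**The concern.** To become an event for B, a member must develop pneumococcal CAP, be tested, and test positive. The vaccine is meant to act on the first step. The second is a clinician's decision at the episode, and it plausibly follows severity and admission. The vaccine may alter severity, since the Objectives list effectiveness against death, ICU admission and length of stay. The vaccination programme described in the Background was also directed at older people and those with high-risk conditions, so the groups may differ in ways that affect how thoroughly a pneumonia is worked up.

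If testing differs between the groups, fewer tests among vaccinated cases look like protection and more tests hide it. A larger cohort does not shrink this bias. B is the pneumonia outcome closest to the vaccine's target, so readers may give it weight despite its secondary status. As the outcome is defined, they could not tell fewer pneumococcal cases from fewer tests.

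**Working it through.** **The plan's own figure.** No power or precision is stated for B. The nearest figure, under Rationale for sample size, is 80% power for 20% effectiveness against CAP. With 13,500 per group, 2.5 years and a two-sided 5% level, it reproduces: 79.1% if 10 per 1000 is the unvaccinated rate, 83.2% if it is the whole-cohort rate. It does not bear on B except as a yardstick for effect size.

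**Expected cases.** CAP: 27,000 × 2.5 × 10/1000 = 675. The Background puts about 50% of CAP down to pneumococcus: 675 × 0.5 ≈ 338.

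**Formula.** For a rare outcome, with equal test sensitivity in both groups, let r be the probability of being tested among vaccinated pneumococcal CAP cases divided by that among unvaccinated ones, given the model covariates. Then

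apparent HR = true HR × r, and apparent VE = 1 − (1 − true VE) × r.

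**Illustrations.** The article gives no testing shares, so these are assumptions spanning a range.

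| Tested, unvaccinated | Tested, vaccinated | r | Apparent VE if true VE is 0% | Apparent VE if true VE is 20% |
|---|---|---|---|---|
| 60% | 60% | 1.000 | 0% | 20% |
| 70% | 65% | 0.929 | 7.1% | 25.7% |
| 60% | 50% | 0.833 | 16.7% | 33.3% |
| 50% | 60% | 1.200 | -20% | 4% |
| 60% | 40% | 0.667 | 33.3% | 46.7% |
| 40% | 60% | 1.500 | -50% | -20% |

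**A route through admission.** Assume 80% of admitted and 20% of outpatient CAP cases are tested. With 70% of unvaccinated and 60% of vaccinated cases admitted, the tested shares are 0.8 × 0.7 + 0.2 × 0.3 = 62% and 0.8 × 0.6 + 0.2 × 0.4 = 56%, so r = 0.903. A vaccine with no effect on B shows 9.7%, and a true 20% shows 27.7%. With the admission shares swapped, r = 1.107 and the results are -10.7% and 11.4%.

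**Against random error.** SE(log HR) ≈ 2/√D. For an assumed D of 100 to 200 identified cases it is 0.20 to 0.14. The log shift is |ln 0.833| = 0.182 in the 60/50 example, about one standard error, and |ln 0.903| = 0.102 in the admission example, about half to three-quarters of one.

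**Cost of a test-negative estimate.** Assume half of CAP is pneumococcal, test sensitivity is 60% and true VE is 20%. Per unit of pneumococcal and unit of other CAP in the unvaccinated, detected cases are 0.60 (unvaccinated) and 0.80 × 0.60 = 0.48 (vaccinated). Tested negatives are 1 + 0.40 = 1.40 and 1 + 0.32 = 1.32. The odds ratio is (0.48/1.32)/(0.60/1.40) = 0.85, so a true 20% shows as about 15%.

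**The case against.** **A condensed article may leave this to fuller documents.** The data-collection instrument already takes in clinical and analytical findings, so tests done may be captured. Statistical analysis never mentions B, so scoring untested cases as non-events is an inference. This has weight. But the article itself fixes a definition that an untested case cannot meet and a time-to-first-event model, and together they leave such a case no other place.

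**Covariates absorb part of it.** Age, comorbidities, immune status, prior pneumonia and attendance frequency are listed as covariates, so much of the route through older, sicker vaccinated members may be adjusted away. This stands: only the difference that remains after adjustment matters, and the illustrations do not separate the two. Covariates fixed at study start cannot, however, fully remove a difference arising at the episode through severity or admission.

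**Care is said to be similar across providers.** That statement is general. It names no test and does not speak to vaccination status or to outpatients against inpatients.

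**Stronger readings that a reader might infer.**
- That the HR for B is biased. Nothing in the article shows that testing differs by vaccination status.
- That the pneumonia result as a whole is compromised. All-cause CAP rests on radiograph and record review and does not pass through this step.
- That a test-negative model should replace the cohort HR. It has its own bias towards no effect, of an order similar to the distortion in the milder examples. Adjusting it for care setting may also condition on something the vaccine changes.

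**Conclusion.** The point holds as a limited one about a secondary outcome. Under the stated definition and model, the VE for pneumococcal CAP equals vaccine protection only if, given the covariates, vaccinated and unvaccinated cases are equally likely to be tested. The article neither ensures this nor provides a way to see it.

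Size and direction are unknown. The illustrated values rest wholly on assumed testing and admission shares, equal test sensitivity, a rare outcome and no allowance for covariate adjustment. A difference of 10 percentage points in testing (60% and 50%) would move a null result to 16.7% or, reversed, to -20%; equal testing would move it not at all. The remedy is cheap and decides what may be concluded about B, so it is worth making.

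**What to change.** 1. In Table 1 B, classify each CAP case as pneumococcal, tested negative or not tested, from the record review and laboratory search already planned.
2. Report the tested share by vaccination status and by hospitalised or outpatient setting.
3. Keep the Cox HR as the main estimate for B.
4. Pre-specify a sensitivity analysis: either a test-negative comparison among tested CAP cases, adjusted for the planned covariates and fitted with and without care setting (a possible mediator), or an analysis weighted for the probability of being tested.
5. State that the VE for B will be read as vaccine protection only if tested shares are similar or the sensitivity analysis agrees.

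The cost is wording, one field for tests done and results, and one extra model; no patient needs an additional test. The drawbacks should be stated with the results: an analysis of tested cases is less precise, and false-negative tests pull the test-negative estimate towards no effect.
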